### Procedure

The intervention study comprises three phases: (1) pre-intervention (baseline) assessments and goal identification, (2) intervention phase, and (3) post intervention assessments.

#### Phase 1: Pre-intervention (Baseline) assessments and goal identification.

The first visit from the placement practitioner will provide an opportunity for the participant to ask questions, and for the practitioner to explain the study procedures and expectations again. If the participant agrees to continue, written informed consent will be obtained. The practitioner will gather baseline data (see Table 1 for list of baseline measures) and discuss possible goals. The first session would be expected to last around 90 minutes. Goal identification can take some time so may occur during the initial visit or in a subsequent visit. The placement practitioner will assist participants and their caregivers in identifying up to three personalized rehabilitation goals using the BGSI. Once goals are identified, the practitioners will work with the participant to operationally define the goals to ensure they are specific, measurable, achievable, relevant and time-oriented (SMART). Practitioners will subsequently work with their clinical supervisors to develop the intervention and session plans, and to determine how best to measure goal performance within sessions.

For the embedded N-of-1 design, baseline data on goal performance will be objectively measured (e.g., proportion of correct responses on a face-name recall goal) with baseline data monitored across three participants concurrently. The participants will be randomly assigned to different baseline durations (see Table 2 for an example). This allows for causal inferences by applying the intervention sequentially to each. An effect replication will be assessed across participants with at least 3–5 data-points per phase.

**Table 2 pone.0322121.t002:** Sample plan for the N-of-1 design showing random allocation of participants to predetermined baseline lengths and random allocation of intervention start-points from a possible two.

Participant # (randomly allocated)	Possible # baseline data points	Possible intervention start points	Actual design – *determined by ExPRT start point randomizer*
3	3/4	4/5	AAAABBBBBBBB
1	5/6	6/7	AAAAABBBBBBB
2	7/8	8/9	AAAAAAABBBBB

#### Phase 2: Intervention.

The intervention will be tailored to each participant’s goals, utilizing techniques from the cognitive rehabilitation literature. The intervention will span approximately six to eight weeks with weekly 60–90-minute sessions, conducted at the participant’s home unless otherwise preferred (option available to conduct sessions in the Memory Clinic). The end of each session will include a review with the caregiver and planning for home practice. Rehabilitative approaches may include compensatory or restorative strategies. Compensatory strategies may include environmental or task modifications, practicing the use of memory aids like diaries, calendars, or medication reminders, or other techniques tailored to the participant’s needs like relaxation. Restorative strategies to support new learning or relearning of functional skills/information may incorporate task analysis, chaining, prompting and fading, multiple exemplar training, mnemonics, errorless learning and/or spaced retrieval. Strategies used during sessions will be documented weekly, and participants will receive a summary report at the end of the intervention. Practitioners will monitor participant’s progress on selected goals during each session to ensure intervention efficacy. For the N-of-1 participants, the intervention start-point will be predetermined (see Table 2) for their goals. The intervention is due to span six to eight weeks but for goals with longer baseline phases this may be less. Intervention length will be determined by participant need, availability and consent to work on goals.

#### Phase 3: Post-intervention outcome measurement.

Standardized outcome measures will be collected to assess the following: the primary outcome, goal attainment and satisfaction (BGSI); and the secondary outcomes, quality of life (QoL-AD) and cognitive function (MoCA). A follow-up meeting will then be arranged for 6-weeks post intervention to collect the final set of outcome measures. Outcome measures will be collected using an assessment booklet, which includes all relevant measures for each time point. The research coordinator will verbally administer the questionnaires and record all responses in the paper assessment booklets.

### Proposed analytic approach

Descriptive statistics will be calculated to compare scores on primary and secondary outcomes at baseline, post-intervention, and at six-week follow-up for all participants who receive CR (n=36). For the embedded *N*-of-1 study, visual analysis will objectively examine the level, trend, and variability of data within each phase, as well as the immediacy of effect and percentage of non-overlapping data. If evidence of an intervention effect is observed, effect size estimates will be calculated. Then, ExPRT (Excel Package of Randomization Tests) software will be used to analyze the randomized single-case multiple-baseline data, providing graphical representation and effect size estimates [38]. The design includes three multiple-baseline design tiers and two potential intervention start-points per tier. The two most extreme mean phase-difference outcomes in the predicted direction will yield a statistically significant result at the.05 level [30].

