## Sub-study 1 – Cognitive rehabilitation intervention

### Participants

This study will include 36 participants with dementia, recruited through the Regional Specialist Memory Clinic (RSMC) at Tallaght University Hospital in Dublin, Ireland. Inclusion criteria specify that participants must have a diagnosis of early-stage dementia, exhibit mild-to-moderate cognitive impairment, be able to provide informed consent, and have a carer willing to provide support. Characteristics associated with positive outcomes in GREAT-CR trials [6] will also be considered for recruitment. These characteristics include being recently diagnosed, able to engage in daily activities and converse about them, motivated to reduce the impact of cognitive impairment on daily life, reasonably active, and supported by a carer who can encourage practice between sessions. Participants lacking the capacity to provide informed consent will be excluded from the research.

### Design and materials for sub-study 1

A quantitative pre-post design with and an embedded randomized *N*-of-1 SCED will be used. For all thirty-six participants, data on the primary outcome of goal attainment and satisfaction, and secondary outcomes of quality of life and cognition will be gathered at baseline, post intervention, and at a six-week follow-up. A subset of three participants will be randomly selected for the SCED analysis to evaluate the impact of GREAT-CR on objective measures of goal attainment. The SCED and reporting will adhere to the What Works Clearinghouse (WWC) Technical Documentation for SCDs [28] and the Single-Case Reporting Guideline in Behavioral Interventions [29]. A randomized multiple-baseline design will determine whether a causal relationship exists between the GREAT-CR intervention (independent variable) and the primary outcome of goal attainment (dependent variable). A multiple-baseline-across-participants approach will be utilized, where behavior on a specified goal will be assessed across three separate participants (e.g., [7]). We include both within-case (phase) randomization and start-point randomization [30]. As per WWC guidelines, an effect replication will be assessed across three participants, with three to five data points per phase (baseline and intervention). Interobserver agreement (IOA) will be collected by two independent assessors for each dependent variable.

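### N-of-1 effect sizes are made conditional on first seeing an effect in the same data, and the text leaves unclear whether the randomization test is conditional too

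*Protocol article*

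**What the plan says.** Under Design and materials for sub-study 1: "A subset of three participants will be randomly selected for the SCED analysis". Under Phase 1: "The participants will be randomly assigned to different baseline durations". Table 2 gives a sample plan with 12 observations per participant and baselines of 4, 5 and 7 points; its first row is "AAAABBBBBBBB".

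The Proposed analytic approach then sets out three steps for these data:

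1. Visual analysis of level, trend and variability within each phase, "as well as the immediacy of effect and percentage of non-overlapping data". No threshold is given for any of these features or for the overall judgement.
2. A conditional step: "If evidence of an intervention effect is observed, effect size estimates will be calculated".
3. A sentence opening with *Then*, under which the ExPRT software "will be used to analyze the randomized single-case multiple-baseline data, providing graphical representation and effect size estimates". This sentence carries no condition of its own.

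The section closes with the design, "The design includes three multiple-baseline design tiers and two potential intervention start-points per tier", and the decision rule, "The two most extreme mean phase-difference outcomes in the predicted direction will yield a statistically significant result at the.05 level".

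**The concern.** Step 2 is a stated rule, not a detail left to another document. Whether an effect is estimated depends on whether the same observations already look like an effect. Chance variation that makes a series look favourable also raises its estimated effect. Estimates that survive such a screen are therefore too large on average, and series that fail contribute none at this step.

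Step 3 can be read in two ways. If *Then* continues the condition, the randomization test and its effect sizes are also produced only after a favourable visual result. If step 3 always runs, ExPRT gives unscreened effect sizes for everyone, and step 2 is either redundant or creates a second, selectively reported set.

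This component carries the causal claim in an otherwise uncontrolled pre-post study, and it has three participants. One withheld estimate is a third of the evidence.

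**Working it through.** **The plan's own figure.** Table 2 allocates participants at random to three tiers and picks one of two start points in each. The number of possible randomizations is 3! × 2³ = 6 × 8 = 48. The second most extreme outcome has p = 2/48 = 0.0417, and the third has 3/48 = 0.0625. Exactly two outcomes therefore qualify at one-sided .05, so the stated rule reproduces.

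**Selection effect on the estimates.** The protocol gives no effect size, autocorrelation or visual threshold, so all three are assumed. The inputs are:

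- Table 2 sample plan: 4+8, 5+7 and 7+5 points.
- Unit within-phase SD and the same true shift in every tier.
- Lag-1 autocorrelation of 0 or 0.3.
- Effect measured as the mean phase difference averaged over the three tiers.
- Visual pass defined as mean PND across tiers of at least 50%, in 100,000 simulated data sets per setting.

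| True shift (SD) | Mean if always reported | Pass rate, autocorr. 0 | Mean after passing | Pass rate, autocorr. 0.3 | Mean after passing |
|---|---|---|---|---|---|
| 0 | 0.00 | 0.7% | 0.72 | 2.1% | 0.81 |
| 0.5 | 0.50 | 7.9% | 0.97 | 14% | 1.04 |
| 1.0 | 1.00 | 36% | 1.25 | 44% | 1.30 |
| 2.0 | 2.00 | 95% | 2.02 | 95% | 2.03 |

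With autocorrelation 0.3, a true 0.5 SD is roughly doubled (1.04/0.5 = 2.08) and a true 1 SD is overstated by 30%. Letting the baselines vary over all 48 randomizations gives the same 1.04 and 1.30.

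**Sensitivity to the assumed screen** (autocorrelation 0.3):

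- Stricter, mean PND of at least 70%: 1.35, 1.57 and 2.15 for true shifts of 0.5, 1 and 2 SD.
- Lenient, passing on any positive mean difference: 1.01 for a true 1 SD.

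**Effect on the test, if it is gated.** For any gate, P(pass and p ≤ .05) ≤ P(p ≤ .05) ≤ 2/48 = 0.0417, so overall type I error cannot rise. The error rate among reported results does change. With no true effect and the 50% screen, the two-most-extreme rule rejects in about 22% of data sets that pass (autocorrelation 0) or 18% (autocorrelation 0.3). In the latter case the joint probability is about 2.1% × 18% ≈ 0.4%, far below 4.17%.

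**PND and baseline length.** PND counts intervention points beyond the best baseline point. With n_A exchangeable baseline points and no ties, an intervention point is the largest of n_A + 1 with probability 1/(n_A + 1), which is the no-effect expectation. For baselines of 4, 5 and 7 this gives 1/5 = 20%, 1/6 = 16.7% and 1/8 = 12.5%. A uniform 1 SD shift (autocorrelation 0) gives expected PND of 49%, 45% and 39%. What matters is the length of the baseline phase; the total number of points is 12 in every tier.

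**The case against.** The strongest reply is that the ExPRT sentence is unconditional as written and itself promises effect sizes. On that reading every N-of-1 participant gets an unscreened estimate, and any bias is confined to the set in step 2. This stands: a reader might infer that effect sizes exist only after a positive visual result, but the text does not settle that. Nor do null cases go without any numbers, because the visual stage is unconditional and yields phase levels and PND.

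A reader might also infer that a gated randomization test is invalid. The inequality above shows otherwise: the gated procedure is conservative overall. What suffers is the meaning of a p-value reported after passing, and the reporting of results that fail.

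The size of the bias rests on a screen that the protocol does not define. PND is one of five listed features, judged together, and the bias is close to nil at a true 1 SD under a lenient screen, or at 2 SD under the 50% screen. This also stands. The direction is upward for any screen that favours larger apparent effects; the amount is not known.

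Finally, it is tempting to say that PND must be replaced. It is a descriptive aid here, while the test statistic is the mean phase difference. The no-effect values are all well below 50%, and ties in a proportion-correct outcome would lower them further. Replacing it is a preference. The whole point concerns three participants in a pilot; the descriptive analysis of all 36 is unaffected.

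**Conclusion.** The concern holds in limited form. The protocol states a rule that makes N-of-1 effect-size calculation depend on a favourable look at the same data, and it leaves open whether the ExPRT analysis shares that condition. Followed literally, the rule produces estimates that are too large when the true effect is small to moderate. The average of 1.30 for a true 1 SD illustrates this under an assumed PND screen and autocorrelation; it is not a forecast for this study. The two-outcome significance rule is correct and is unaffected if the test is always run. This should be corrected because the ambiguity touches the study's one causal analysis, but it does not undermine the design.

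**What to change.** Replace the conditional sentence in the Proposed analytic approach with: *Effect size estimates and the ExPRT randomization test will be calculated and reported for all three N-of-1 participants regardless of the visual analysis.* This settles both readings and leaves the visual analysis in place.

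Keep PND if wanted, with a note that its no-effect expectation falls as the baseline gets longer, so values from different tiers are not directly comparable. Adding an all-pairs overlap index, whose no-effect value is 50% at any phase length, is optional.

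The cost is one sentence and a trivial amount of extra calculation. Data collection, randomization and sample size do not change.

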## Sub-study 2 – mixed methods implementation evaluation

### Participants

In sub-study 2, purposive sample of key stakeholders will include a subset of participants with dementia from group 1 in the sub-study 1 (n= 6–10) and family carers (n= 6–10) engaged with the intervention, placement practitioners (n= 3–5), placement supervisors (n= 3), and clinical and managerial staff at the pilot site (n=3–5). Participants with dementia who have taken part in the CR intervention as part of sub-study 1 and family carers of these participants (aged 18 and above) will be offered as opportunity to take part in the interviews. Also, trainee psychologists who have completed the 9-month clinical placement at the RSMC as part of this study will be interviewed. Psychologists providing clinical supervision to these trainees, specifically members of the project team, will also be included. Lastly, clinical and managerial staff at the memory clinic involved in the delivery of services to people with dementia will be part of the qualitative interviews. Participants under the age of 18 will be excluded from sub-study 2.

### Design and materials of sub-study 2

This sub-study 2 will employ a mixed-methods implementation evaluation to assess the feasibility, acceptability, appropriateness, and potential sustainability of the implementation model. Both qualitative and quantitative data will be collected at the organizational, practitioner, and service-user levels. Semi-structured interviews will be conducted with stakeholders described above. Framework analysis [25] will inform development of the interview guides, data collection, and analysis. The analyst will familiarize themselves with the transcripts, and data will be systematically coded using a matrix to summarize data by case and by code. Comparison of codes across and within cases will be used to identify and refine themes using a combination of inductive and deductive processes; themes will be mapped to pre-defined constructs proposed to influence implementation (identified from relevant implementation frameworks) while also allowing scope for unanticipated themes to be identified inductively. Following guidelines for framework analysis, two researchers will independently code the first few transcripts; the research team will then review initial codebooks to agree the analytical framework (set of codes) that will be applied to the remaining interviews. An iterative process will be used to review codes, themes, and findings, with any differences of opinion regarding the interpretation of findings resolved through discussion by the research team.

Quantitative indicators of implementation success will be derived by assessing outcomes against specified targets and analyzed descriptively to support the qualitative findings related to each implementation outcome. The key implementation outcomes selected for evaluation are outlined in Table 3.

**Table 3 pone.0322121.t003:** Sub study 2 implementation outcomes.

Outcome	Outcome Definition (12)	Research Question
Feasibility	Extent to which the innovation can be practically used in a given setting	Can a supervised placement model be utilised in memory services to increase availability of CR for people with early-stage dementia?
Acceptability	View among stakeholders that the given innovation is agreeable or satisfactory	Is the proposed model of intervention delivery acceptable for people with dementia, their families, trainees, and service providers?
Appropriate-ness	Perceived compatibility with needs and practices of a setting or population; perceived utility in addressing a given problem	Is CR impactful for people with dementia; does it improve functional outcomes?
		Does the implementation model effectively address the needs of the stakeholders?
(Potential) Sustainability	Extent to which the innovation is maintained or routinised within a setting over time	Can the placement model be managed effectively within the memory services?
		Do clinical and managerial staff intend to maintain the intervention and placement model going forward?
		What barriers and facilitators affect the implementation of CR using the supervised placement model?

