### Procedure

#### Groups 1 and 2: Participants with dementia who received CR intervention and family members/caregivers.

A subset of 6–10 participants with dementia from sub-study 1 and a subset of 6–10 family members/caregivers supporting participants in sub-study 1 will be invited for qualitative interviews to evaluate the implementation. Interviews, conducted by the research coordinator, will focus on participants’ and family members’ experiences with the CR intervention. Interviews will be semi-structured, based on existing literature and frameworks, lasting 30–60 minutes, and will be recorded and transcribed for analysis.

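### The trainee interviews in sub-study 2 are described for placement completers only, which leaves that small strand open to completer bias; the analysis role of the interviewed supervisors is also left open

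*Protocol article*

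**What the plan says.** All references are to the protocol article.

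- **Trainees.** Under sub-study 2, Participants: "trainee psychologists who have completed the 9-month clinical placement at the RSMC as part of this study will be interviewed". The procedure text for Groups 3, 4 and 5 plans 3 to 5 practitioner interviews with a subset of the practitioners and gives no completion condition.
- **Supervisors.** The same Participants section states: "Psychologists providing clinical supervision to these trainees, specifically members of the project team, will also be included". Three are planned.
- **Other informants.** The procedure for Groups 1 and 2 plans "A subset of 6–10 participants with dementia from sub-study 1 and a subset of 6–10 family members/caregivers". Three to five clinical and managerial staff complete the sample.
- **Analysis.** Under Design and materials of sub-study 2, "two researchers will independently code the first few transcripts". The research team then agrees the set of codes, with "any differences of opinion regarding the interpretation of findings resolved through discussion by the research team".
- **Questions to be answered.** For acceptability, Table 3 asks: "Is the proposed model of intervention delivery acceptable for people with dementia, their families, trainees, and service providers". Under sustainability it asks whether the placement model can be managed within the service, whether clinic staff intend to keep it, and what helps or hinders it.

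**The concern.** Completing a nine-month placement is itself partly a sign that the placement model worked for that trainee. Choosing trainee informants on completion is therefore selection on something close to the outcome. A trainee who left because the arrangement was unworkable could speak directly to three of the Table 3 topics: acceptability to trainees, manageability of the placement, and barriers. The Information power section justifies small samples by how much relevant information the informants hold, and leaving out possible negative cases weakens that argument.

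The supervisors raise a second, smaller issue. They report on a model run by their own project team, and under Phase 1 of the sub-study 1 procedure they also help practitioners to develop the intervention and session plans. The article does not say whether they take part in interpreting the interviews.

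Under Anticipated implications, guidelines for scaling up the model nationally are to follow from the findings. Both features would push in the favourable direction if they operate.

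**Working it through.** The plan gives no figure to reproduce here: sub-study 2 is qualitative and descriptive, with no power or error-rate calculation. The check compares the sections and sizes the strands.

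**Step 1. Who is eligible, section by section.**

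| Group | Participants section | Procedure section | Early leavers covered? |
|---|---|---|---|
| Trainees | Completed the placement | Subset of practitioners, no condition | Not under the first; not stated under the second |
| People with dementia | Took part in the intervention | From sub-study 1, received the intervention | Yes, neither text requires completion |
| Carers | Carers of those participants | Supporting sub-study 1 participants | Yes, on the same reading |

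Only the trainee group carries a completion condition.

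**Step 2. Weight of the two strands.** Inputs are the planned numbers: people with dementia 6–10, carers 6–10, trainees 3–5, supervisors 3, staff 3–5.

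- Total: 6 + 6 + 3 + 3 + 3 = 21 at the minima; 10 + 10 + 5 + 3 + 5 = 33 at the maxima.
- Trainees plus supervisors: 3 + 3 = 6 to 5 + 3 = 8. The other three groups: 15 to 25.
- Share at matched minima: 6/21 = 29%. At matched maxima: 8/33 = 24%.
- Smallest share: 6/(6 + 25) = 6/31 = 19%. Largest share: 8/(8 + 15) = 8/23 = 35%.
- The other three groups therefore supply 65% to 81% of interviews.
- Supervisors alone: 3/33 = 9% to 3/21 = 14%.

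**Step 3. What completer selection could do within the trainee strand.** Let c be the completers interviewed and d the trainees who left. As an illustration, assume that all completers find the model acceptable, that all leavers do not, and that all could be interviewed. Completer-only interviews then show 100% acceptance, while the share among all c + d trainees is c/(c + d). The article gives neither the number of trainees starting nor the number expected to leave, so d is an assumption.

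| c | d = 0 | d = 1 | d = 2 |
|---|---|---|---|
| 3 | 100% | 3/4 = 75% | 3/5 = 60% |
| 4 | 100% | 4/5 = 80% | 4/6 = 67% |
| 5 | 100% | 5/6 = 83% | 5/7 = 71% |

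This is a worst-case pattern for each d. A framework analysis does not report a percentage of acceptance; the table only shows how much of a small strand one or two missing voices represent.

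**Step 4. Who interprets.** Supervisors are called members of the project team; disagreements are settled by the research team. The article does not say that the two are the same, and it does not say that they are separate. Independent double coding is stated for the first few transcripts only.

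**The case against.** The strongest case on the other side has four parts.

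1. *The completion condition may not be exclusive.* The text says that completers will be interviewed, the only exclusion stated for sub-study 2 is age under 18, and the procedure section has no completion condition. This stands in part: the two sections can be read differently. But the procedure section does not widen the frame, and the only description of trainee eligibility is completion.
2. *Acceptability and sustainability do not rest on these two groups.* This stands. A reader might infer that completers and insiders decide the verdict. Table 3 puts acceptability to patients, families and service providers as well, one sustainability question concerns clinic staff, and quantitative indicators against targets support the findings.
3. *Respondents judging their own data is an inference.* This also stands. A reader might infer it from the closeness of the two team names, but the article never equates them and names no supervisor as coder or adjudicator. A condensed article may leave the make-up of the analysis team to the full protocol. What remains is a request for one clarifying sentence.
4. *Project-team supervisors follow from the pilot.* They supervise these trainees, and the article describes no independent supervisors of this placement. This stands as a reason to keep their interviews and label them for what they are, not as a reason to drop them.

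A reader might also infer that people with dementia who stopped early are left out. The text does not support that: having taken part is enough.

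**Conclusion.** The point holds in a limited form. As written in the Participants section, trainees who leave the placement early are not interviewed, and the procedure section does not settle the matter. The trainee strand is therefore open to completer bias, with a plausible favourable direction. One unheard leaver would be 25% of the trainee view alongside 3 completers and 17% alongside 5. This rests on an assumed withdrawal, since none is given, and the bias is zero if all trainees complete.

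The supervisor issue is secondary: the supervisors are insiders by the article's own description, and no stated rule keeps them from interpreting their own interviews, but nothing says that they do so.

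A reader might go further and conclude that the overall verdict of sub-study 2 is tilted upward. The article does not support that. The direction is a risk, not a shown result, and 65% to 81% of the interviews come from groups with no completion condition and no stated project-team membership.

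**What to change.** 1. In the sub-study 2 Participants section, define the trainee informants as those who started the placement instead of those who completed it, and use the same definition in the procedure text for Groups 3, 4 and 5.
2. Under Design and materials of sub-study 2, state that interviewed supervisors do not code or adjudicate the interview data, and that their views are reported as a separate, insider strand.

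No places need to be reserved for people with dementia or carers who stopped early, because they are already eligible. Interviews with people who declined the intervention are not part of this fix: they fall outside the five participant groups set out in Methods and could not be added by a change of wording.

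The cost is a few sentences and no extra interviews. The downside is that early leavers may be harder to recruit, so some trainee places could go unfilled; reporting how many trainees started, left and were interviewed would show this. If no trainee leaves, the first change alters nothing.
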